## Abstract

**Background:**

People with Multiple Sclerosis have a life long need for physiotherapy and exercise interventions due to the progressive nature of the disease and their greater risk of the complications of inactivity. The Multiple Sclerosis Society of Ireland run physiotherapy, yoga and exercise classes for their members, however there is little evidence to suggest which form of physical activity optimises outcome for people with the many and varied impairments associated with MS.

**Methods and design:**

This is a multi-centre, single blind, block randomised, controlled trial. Participants will be recruited via the ten regional offices of MS Ireland. Telephone screening will establish eligibility and stratification according to the mobility section of the Guys Neurological Disability Scale. Once a block of people of the same strand in the same geographical region have given consent, participants will be randomised. Strand A will concern individuals with MS who walk independently or use one stick to walk outside. Participants will be randomised to yoga, physiotherapy led exercise class, fitness instructor led exercise class or to a control group who don't change their exercise habits.

Strand B will concern individuals with MS who walk with bilateral support or a rollator, they may use a wheelchair for longer distance outdoors. Participants will be randomised to 1:1 Physiotherapist led intervention, group intervention led by Physiotherapist, group yoga intervention or a control group who don't change their exercise habits. Participants will be assessed by physiotherapist who is blind to the group allocation at week 1, week 12 (following 10 weeks intervention or control), and at 12 week follow up. The primary outcome measure for both strands is the Multiple Sclerosis Impact Scale. Secondary outcomes are Modified Fatigue Impact Scale, 6 Minute Walk test, and muscle strength measured with hand held dynamometry. Strand B will also use Berg Balance Test and the Modified Ashworth Scale. Confounding variables such as sensation, coordination, proprioception, range of motion and other impairments will be recorded at initial assessment.

**Discussion:**

Data analysis will analyse change in each group, and the differences between groups. Sub group analysis may be performed if sufficient numbers are recruited.

**Trial registration:**

ISRCTN77610415

## Background

Multiple sclerosis (MS) is a demyelinating, degenerative disease of the central nervous system. It can cause a multitude of motor, sensory, visual, psychological, sexual, and bladder and bowel symptoms. Europe has the highest estimated prevalence of MS in the world at 80 per 100,000[1] and in Ireland people with MS (PwMS) make up the largest diagnostic group (9.2%) of those registered on the National Physical and Sensory Disability Database[2]. MS is a progressive disease that can lead to disability, functional limitations and a poor quality of life (QoL). In a recent profiling study[3], 59% of the people with MS had EDSS scores between 0 and 4.0, 18% had scores of 6.0 ± 6.5, and 6% had a score of 8.0. It is suggested that within 15 – 25 years of diagnosis nearly 50% of PwMS will reach an EDSS score of at least 6 meaning they will require the use of a walking aid[4,5]. PwMS have a normal life expectancy, therefore, they may have to live for many years with severe mobility problems and have a need for regular therapeutic intervention. Therefore the importance of appropriate and timely intervention in patients with relapsing disease to slow or prevent the accumulation of physical disability associated with progressive types of disease is apparent.

There is a significant body of evidence to suggest that exercise programmes have a beneficial effect on both disease symptoms and general fitness of people with MS who are ambulatory [6]. The authors recommend that future studies should adhere to methodological principles of allocation concealment, blind recording and description of dropouts.

A meta-analysis of physical activity levels of people with MS concluded that they engage in significantly less physical activity than non-diseased populations[7]. In a study investigating coronary heart disease risk in women with MS, those who had higher levels of leisure time physical activity had a lower risk of secondary disease[8] and ambulatory women with MS who took part in a resistance training programme also had a decreased risk of coronary artery disease[9]. A meta analysis of the relationship between exercise and quality of life for people with MS suggested that quality of life can be optimally improved through exercise programmes less than three months duration, involve greater than 90 minutes a week, and be evaluated using MS specific measures[10]. Given the positive relationship between physical activity and improving disease symptoms and quality of life, and reducing secondary disease, it is essential that the optimal physical activity programmes are identified.

In physiotherapy practice it is acknowledged that people with differing levels of mobility will have varying treatment needs therefore the literature has been separately reviewed for those with an EDSS of 0–6 and for those with an EDSS of >6.

The literature published since the Cochrane review[6] on the specific benefits of physiotherapy and exercise interventions for PwMS with an EDSS of 0–6 suggests that aerobic exercise positively influences fitness, walking speed, gait parameters, disability, fatigue and quality of life [11-16]. Additionally, Progressive Resistance Exercise (PRE) improved strength, walking over short distances, improved stepping time, improved fatigue and reduced the physical impact of MS[16]. However, there was only one intervention followed up at three months [17-20] and this found that benefits were maintained for the Functional Assessment of MS and the MSIS-29 only.

Several studies have combined aerobic exercise and PRE, [21] and have reported no deleterious effects. However, the intervention has been delivered as a home exercise programme, bringing into question the issue of compliance.

To date, a lot of studies considering exercise interventions for people with an EDSS of < 6 have a moderate to high risk of bias – mostly due to lack of blinding or not having a control group, questioning the validity of the results. More rigorous methodologies are needed to eliminate this bias and allow firm conclusions to be drawn.

Yoga is frequently provided to its members by MS Society of Ireland (MSI) and has been show to be feasible in this population[22] however, only one small scale study has evaluated it.

It is possible that the exercise needs of this group of PwMS can be met by fitness instructors in gyms providing a non medical environment for exercise participation. This study therefore aimed to assess the effect of intervention delivered by fitness instructors, following assessment by a physiotherapist to ensure that no impairments existed that would prevent this.

A review of the literature for those with an EDSS score > 6 suggests that a multitude of interventions can be beneficial in this population. These include physiotherapy, aerobic exercise and strength exercise. It is unclear, however, to what extent the results can be applied to PwMS with an EDSS score of >6 as PwMS with EDSS scores of between 1 and 6.5 were given the same interventions even though their treatment needs vary greatly. The positive outcomes were specific to the intervention used, for example, balance rehabilitation showed improvements in balance scores [12] and aerobic exercise showed improvements in fitness levels[23]. The optimal type of intervention and its frequency and duration for this population is, however, still unknown and further research is needed to develop treatment recommendations for clinicians treating PwMS with more severe mobility problems. In completing a large multi centre trial it may be possible to examine the subgroups of individuals with specific needs to establish what intervention is best for which sub groups of people with differing impairments in order to allow clinicians to deliver the optimal intervention to match the differing impairments.

The Getting the Balance Right (GTBR) projects is a collaboration between the Physiotherapy Department of the University of Limerick, and MSI that aims to both deliver and evaluate physiotherapy and exercise interventions for people with MS. There are many unknown variables to be examined in this population, therefore in order to determine the research questions with the highest priority a group of physiotherapists specialising in MS, the regional offices of MSI and the latest findings from the literature were consulted. The conclusions of this consultancy period was that the overarching question was what exercise interventions should MSI provide for their members in order to optimise function, reduce fatigue and increase quality of life.

## Methods and design

### Design

This will be a multi-centre, prospective, single blinded, block randomised controlled trial. Participants will be stratified according to mobility level using the mobility section of the Guys Neurological Disability Scale[24]. Those who score 0, 1 or 2 are stratified to stand A, those scoring 3 and 4 to strand B. For each strand blocks of subjects will be randomised to one of the interventions or to the control group.

Strand A will concern individuals with MS who walk independently or use one stick to walk outside. The objective is to compare the immediate and long term effect of yoga, physiotherapy led exercise class, fitness instructor led exercise class to a control group who don't change their exercise habits.

Strand B will concern individuals with MS who walk with bilateral support or a rollator, they may use a wheelchair for longer distance outdoors. The objective is to compare the immediate and long term effect of 1:1 Physiotherapist led intervention, group intervention led by Physiotherapist, or group yoga intervention to a control group who don't change their exercise habits.

The study protocol was approved by 10 regional ethics committees in the Republic of Ireland

### Participants

Anyone with a diagnosis of MS confirmed by their consultant physician or neurologist, resident in the republic of Ireland is eligible to take part. It is not necessary for participants to be members of MSI.

People with MS will be excluded from the study if they are currently experiencing an exacerbation of symptoms due to relapse, have had steroid treatment within 3 months of the baseline measurement, are pregnant at the time of referral, or are under 18 years of age

### Recruitment and Randomisation

Participants can be referred to the project by themselves, their carer, MSI, Chartered Physiotherapists, Neurologists, GPs or Clinical nurse specialists.

Referral will be made to the ten regional offices of MSI. A form completed over the telephone will be used to screen for exclusion criteria and to stratify according to mobility level. Participants will then be sent the information leaflet for the relevant strand and a consent form. The consent form will be returned to the regional office and consenting subjects will be coded by region, number and then strand (e.g. MW1A, MW2A, MW3B...). The participants General Practitioner will be sent a letter informing them of their participation and enclosing the relevant information leaflet. Once consent for 8 people of a strand is obtained, the regional office will contact the National Coordinator who will allocate that block of subjects to the control or an intervention condition. Block randomisation was done using a sealed enveloped with pieces of paper with the four groups written on them. The paper chosen will be emitted each time until four groups are chosen to ensure even numbers of groups. When the fifth group is ready to go, all the pieces of paper will be returned to the envelope, and so on. The order of allocation to control or intervention will be concealed from the regional offices until they have scheduled that block of 8 people for assessment.

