### Sample size calculations

#### Strand A

Based on a pilot study and the MSIS physical component scores then a sample size of 60 in each group will be sufficient to show a similar probability (0.329) that an observation after intervention will be less than before intervention as in the pilot study (mean before intervention 62.4, after intervention 53.6). This is based on using the Wilcoxon Signed Rank Test, significance level 0.05 and a power of 90%.

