### Statistical Analyses

All measures will be summarised and tested for normality. If variables are non-normal then Wilcoxon Signed Rank tests will be used to test for differences before and after interventions and Mann-Whitney U tests will be used to test for differences between groups before and after interventions. If the variables are reasonably normally distributed then repeated measures ANOVA will be carried out to test for differences between groups and over time. Suitable plots will be used to demonstrate the changes found.

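### Regional blocks of 8 are allocated whole to one arm, which is cluster randomisation, but the sample size and every named test treat participants as independent

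*Protocol article*

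**What the plan says.** The Design section makes the block the thing that is randomised: "For each strand blocks of subjects will be randomised to one of the interventions or to the control group". Recruitment and Randomisation gives the mechanics. "Once consent for 8 people of a strand is obtained", the region contacts "the National Coordinator who will allocate that block of subjects to the control or an intervention condition". Four slips, one per condition, are drawn without replacement and then refilled: "When the fifth group is ready to go, all the pieces of paper will be returned to the envelope". The word group in that sentence shows that one slip serves eight people, not one. The abstract adds that a block shares a strand and a region: "Once a block of people of the same strand in the same geographical region have given consent, participants will be randomised".

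For Strand A, Sample size calculations states that "a sample size of 60 in each group will be sufficient", based on a "similar probability (0.329) that an observation after intervention will be less than before intervention", significance level 0.05 and 90% power. Strand B gives 22 per group from a probability of 0.217 in the same way. Neither mentions an ICC or a design effect.

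Statistical Analyses names Wilcoxon signed rank and Mann-Whitney tests for non-normal variables. Otherwise "repeated measures ANOVA will be carried out to test for differences between groups and over time". No term for block, region or class appears.

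**The concern.** Block randomised normally means that individuals are allocated in permuted blocks. Here the block itself is allocated, so the independent units are the blocks: 60/8 = 7.5 per arm in Strand A and 22/8 = 2.75 in Strand B (8 and 3 in practice).

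People in one block share a region. In the class arms (three in Strand A, two in Strand B) they also share an instructor and classmates. The yoga and fitness-instructor content is deliberately left unspecified, so it can differ between instructors. If outcomes within a block are positively correlated, tests on individuals give standard errors that are too small, and a regional or class effect can pass for a programme effect. The trial is meant to tell MS Ireland which programme to deliver, so this bears directly on its conclusion. In Strand B, with about three blocks per arm, one unusual block can decide an arm's result.

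**Working it through.** **Inputs.** Block size 8 (Recruitment and Randomisation); 60 and 22 per group, probabilities P = 0.329 and 0.217, alpha 0.05, power 90% (Sample size calculations). The ICC is not in the document, so 0.01, 0.05 and 0.10 are assumed. The relevant ICC is that of the quantity analysed, such as change from baseline.

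**Step 1: reproduce the plan's numbers.** Noether's formula for two independent groups of equal size, two-sided alpha 0.05, 90% power:

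N total = (1.960 + 1.282)² / [3 (P − 0.5)²] = 10.507 / [3 (P − 0.5)²]

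- Strand A: 10.507 / (3 × 0.171²) = 119.8, so 59.9 per group, rounded up to 60.
- Strand B: 10.507 / (3 × 0.283²) = 43.7, so 21.9 per group, rounded up to 22.

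Both match, which leaves no room for a design effect. The article attributes these numbers to a before/after signed rank test, but they reproduce only as a two-group calculation. That is a separate matter; below, P is read as the two-group probability.

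**Step 2: design effect, effective size and true type I error.** DE = 1 + (8 − 1) × ICC; effective n = n/DE; true error of the unadjusted test = 2 × [1 − Φ(1.96/√DE)].

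| ICC | DE | Effective n, A | Effective n, B | True type I error |
|---|---|---|---|---|
| 0.01 | 1.07 | 56 | 21 | 5.8% |
| 0.05 | 1.35 | 44 | 16 | 9.2% |
| 0.10 | 1.70 | 35 | 13 | 13.3% |

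A simulation of the Mann-Whitney test (10,000 runs per setting, blocks of 8) gave 5.5%, 8.7% and 13.0% with 8 blocks per arm, and 5.5%, 8.7% and 12.8% with 3.

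**Step 3: power with a block-level error term.** For normal data P corresponds to d = −√2 × Φ⁻¹(P), which is 0.626 in A and 1.106 in B. The noncentrality is d / √(2 DE/n). With error pooled over four arms, the degrees of freedom are 4 × (8 − 1) = 28 in A and 4 × (3 − 1) = 8 in B.

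| Basis | ICC 0.01 | ICC 0.05 | ICC 0.10 |
|---|---|---|---|
| A, 60 per arm | 89% | 81% | 72% |
| A, 64 per arm (8 full blocks) | 91% | 84% | 75% |
| B, 22 per arm | 87% | 79% | 69% |
| B, 24 per arm (3 full blocks) | 90% | 82% | 73% |
| B, 24 per arm, only the two compared arms (4 df) | 79% | 70% | 60% |

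On the last basis Strand B has only about 81% power even at ICC 0.

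**Step 4: numbers needed to keep 90%.** Multiplying by DE alone, before rounding to whole blocks and before any small-sample allowance: Strand A 60 × 1.35 = 81 and 60 × 1.70 = 102; Strand B 22 × 1.35 = 29.7, so 30, and 22 × 1.70 = 37.4, so 38 per arm.

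**The case against.** The strongest reply is that the size of the problem rests on an ICC the document does not give. At 0.01 the error rate is only 5.8%, and with full blocks the power is essentially the stated 90%. The planned tests also look at change over time, which removes stable differences between regions, so the ICC that matters may be small. This is fair, and it is why the result is shown as a range. It does not make the analysis correct: the plan allows for no correlation at all, and a shared class, instructor and region make a positive value plausible.

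Three narrower points also stand.

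- Strand B's third intervention is one-to-one physiotherapy and the controls attend no class, so class effects do not arise in every arm. Region is still shared.
- Participant codes hold region, number and strand, not block, so block membership has to be kept from the allocation record.
- The abstract's statement that participants will be randomised could suggest individual allocation, but the Design and Recruitment sections settle the mechanism the other way.

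Nor is this a detail left to a fuller document. The article itself fixes the unit of allocation, the sample sizes and the tests, and they do not fit together.

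**Conclusion.** The concern holds and should be corrected before analysis. The trial is cluster randomised in blocks of 8, while its sample size and named tests are those of an individually randomised trial. If the ICC lies between 0.01 and 0.10, between-group tests at a nominal 5% have a true error rate of roughly 6% to 13%. A valid block-level analysis at the planned numbers has power of about 89% down to 72% in Strand A and 87% down to 69% in Strand B. These figures assume blocks of 8, normal outcomes, the plan's probabilities read as two-group effects, and an error term pooled over four arms. Comparing only two arms at a time makes Strand B clearly worse. At the bottom of the ICC range the practical loss in Strand A is small.

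**What to change.** - Describe the design as cluster randomised, with regional blocks of 8 as the unit, in the abstract, the Design section and Recruitment and Randomisation.
- Record a block identifier for every participant from the allocation record.
- Replace the individual-level tests with one linear mixed model per strand: all four arms as a fixed effect, baseline MSIS as covariate, block as random intercept, and Kenward-Roger degrees of freedom. An analysis of block-level summaries is an acceptable alternative; either way the small-sample correction matters most in Strand B.
- Restate the power for 60 and 22 per group after a design effect of 1 + 7 × ICC, over a stated ICC range, and report the observed ICC with the results.

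The cost is rewording, one extra data field and a less favourable power statement. No extra patients are needed if that lower power is accepted. Keeping 90% would take at least 81 per arm in Strand A and 30 in Strand B at ICC 0.05, before rounding up to whole blocks.

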### Assessment

Each participant will be assessed by a blinded assessor who is unaware of group allocation. Assessors will attend training days in order to standardise the measurements.

Assessments will be carried out at baseline (week 1), post-intervention (week 12) and at follow-up (week 24). The following outcome measures will be used for all three assessments: Multiple Sclerosis Impact Scale 29 version 2 (MSIS), Modified Fatigue Impact Scale (MFIS), six minute walk test (6MWT), physiological cost index (PCI), and hand held dynamometry (HHD). In addition the Berg Balance Scale (BBS) and the Modified Ashworth Scale (MAS) will be used for strand B. As equipment for PCI and HHD are not available to all assessors some participants will not have these measures recorded. The more physically demanding outcome measures were separated to avoid fatigue and so the order of testing for strand A was 6MWT including PCI, MSIS, HHD, MFIS. For strand B it was 6MWT including PCI, MSIS, BBS, MFIS, MAS, HHD

A standardised assessment at baseline considered the participants suitability for exercise and measured confounding variables such as level of sensory loss, coordination deficits etc.

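### A block's allocation is concealed from the regional office only until assessments are booked, so it can be known before the self-reported baseline is complete

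*Protocol article*

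**What the plan says.** Under Recruitment and Randomisation, eligibility is first checked remotely: "A form completed over the telephone will be used to screen for exclusion criteria and to stratify according to mobility level". Written consent follows. Then: "Once consent for 8 people of a strand is obtained, the regional office will contact the National Coordinator who will allocate that block of subjects". All 8 people in the block go to the same condition. The regional office books the assessments, and the order of allocation is "concealed from the regional offices until they have scheduled that block of 8 people for assessment".

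The Assessment section places baseline in week 1. It includes the MSIS and an examination described thus: "A standardised assessment at baseline considered the participants suitability for exercise". Assessors are said not to know the allocation. Under Participants, one exclusion is dated from baseline, not from screening: people are excluded if they "have had steroid treatment within 3 months of the baseline measurement".

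The trial is single blind. The MSIS is the primary outcome in both strands and is the patient's own rating. The Discussion lists concealed allocation among the trial's strengths.

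**The concern.** The stated rule ties the end of concealment to an administrative step, booking, that comes before any outcome has been measured. From then until baseline is finished, the people who took the referrals, hold the consent forms and arrange the visits may know which condition the block has been given. No sentence keeps it from participants during this interval.

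Two things could then depend on the arm. The first is who reaches baseline. Someone who learns that the block is a control block, or has been given an unwanted class, may withdraw or ask to be rescheduled. An informed office may also apply the steroid criterion, which can only be settled at the baseline date, more or less strictly. The second is the baseline MSIS itself. Assessor blinding does not protect a score that the participant supplies, and the planned before/after tests and repeated measures ANOVA both use it. Because a block shares one condition, a single disclosure can affect 8 people in the same direction.

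**Working it through.** **Order of events, from Participants, Recruitment and Randomisation, and Assessment**

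1. Telephone screen and stratification.
2. Information leaflet, then consent.
3. Eight consents in one strand.
4. The National Coordinator allocates the block.
5. The regional office books the 8 assessments.
6. Concealment from the regional office ends.
7. Week 1: baseline MSIS, other measures and the suitability check. Steroid eligibility is also fixed by this date.

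Steps 1 to 3 precede the allocation, so knowledge of the arm cannot influence who makes up the 8. Step 7 follows step 6, so loss before baseline and the baseline score are exposed. The article states no figure for this, so there is none to reproduce.

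**Illustration of size**

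Inputs from the Sample size calculations section:
- Strand A pilot change: 62.4 − 53.6 = 8.8 points; 60 per group.
- Strand B pilot change: 23.0 − 18.8 = 4.2 points; 22 per group.

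Assumption: knowing the arm moves the mean baseline MSIS by d = 1 to 4 points, on the same scale as the pilot means. The article gives no value for d and no direction.

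A shift confined to baseline passes in full into the change: (baseline + d) − post = true change + d.

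| d, whole arm | Strand A, d/8.8 | Strand B, d/4.2 |
|---|---|---|
| 1 | 11% | 24% |
| 2 | 23% | 48% |
| 4 | 45% | 95% |

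If only one block of 8 learns its arm early, the arm mean moves by d × 8/60 = 0.13d in Strand A and d × 8/22 = 0.36d in Strand B. For d = 4 that is 0.53 points (0.53/8.8 = 6%) and 1.45 points (1.45/4.2 = 35%).

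**Which planned analyses carry the shift (Statistical Analyses)**

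- Wilcoxon signed rank, before v after within a group: yes, in full.
- Repeated measures ANOVA, in the contrast of baseline with a later visit: yes.
- Mann-Whitney between groups on post-intervention scores: no, though arm-dependent loss before baseline would still affect it.

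**The case against.** The strongest reply is that allocation concealment exists to protect entry to the trial, and here it does: screening, consent and completion of the 8 all come before the allocation. That stands. A reader might infer that the trial's concealment is undone and the Discussion's claim false. The documents do not support that; the weakness is confined to the interval between booking and the end of baseline.

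Three further inferences also go too far.

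- **That participants know their arm at baseline.** The article speaks only of regional offices and sets the earliest point of release. It neither says that participants are told by then nor prevents it.
- **That the suitability decision or the assessor's blinding is compromised.** Assessors are stated to be blinded, and a blinded judgement should not vary with the arm. The Background does say that fitness-instructor delivery comes "following assessment by a physiotherapist to ensure that no impairments existed that would prevent this", but this is rationale for one intervention. It does not say that other arms skip the check or use another threshold, and unsuitability is not a listed exclusion.
- **That 8.8 is a planned difference between arms.** It is a pilot change within a group, so the percentages above give scale and do not estimate bias in a between-arm contrast.

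It is also fair to say that a condensed article may leave the timing of disclosure to participants to the full protocol. But the article does fix when concealment from the offices ends, and the point rests on that stated rule.

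**Conclusion.** The point holds as a limited, avoidable weakness. Under the rule as written, the regional office may know a block's arm before its baseline MSIS is completed, and the article states no safeguard that keeps it from participants. Losses before baseline and self-reported baseline scores can therefore depend on allocation, with up to 8 people affected together.

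Whether this would happen, in which direction and how strongly cannot be determined from the article. The figures of 11% to 45% (Strand A) and 24% to 95% (Strand B) rest on an assumed 1 to 4 point shift across a whole arm. They apply to before/after changes only, and are smaller if few blocks are affected. The change is worth making because it alters one stated step at little cost, not because bias of that size has been shown.

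**What to change.** Amend Recruitment and Randomisation so that the National Coordinator either draws the block's allocation, or at least withholds the result from regional offices, participants and assessors, until all 8 have completed the baseline assessment including the suitability check. Add that anyone lost after release is counted in the allocated arm. There is no need to require that people lost before release be replaced; that could mean new referrals, consents and assessments while the other baselines age.

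Sample size is unchanged and no visits are added. The cost is shorter notice for booking instructors and venues, and a short gap between baseline and class start. The timetable leaves little slack: with baseline in week 1 and assessment in week 12 after 10 weeks of intervention, classes occupy weeks 2 to 11. If classes must be reserved early, the National Coordinator could do so without telling staff who deal with participants.
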